### 5.1.2 Outcomes of interest

The primary outcome will be a composite outcome of time to COVID-19 hospitalisation or death. COVID-19 hospitalisation will be defined as a RT-PCR confirmed positive test for SARS-CoV-2 in the 14 days prior to admission, or with ICD-10 code for COVID-19 (in any diagnostic position).

COVID-19 deaths will be defined as COVID-19 as the underlying ICD-10 cause of death recorded on the death certificate or death recorded in SIVEP-Gripe^^[[2]](#footnote-1)^^ within 28 days of a confirmed positive test.

Secondary outcomes will be the single outcomes of: i) COVID-19 hospitalisation, ii) COVID-19 deaths, iv) RT-PCR confirmed positive test, provided numbers of events allow. We anticipate the RT-PCR confirmed SARS-CoV-2 infection results to be more susceptible to bias arising from differential ascertainment, and therefore anticipate treating these results as more tentative.

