# Statistical Analyses

### 5.1.1 Exposures of interest

###

Our primary exposure will be receipt of a COVID-19 vaccine booster, with categories to include time since receipt of a booster dose. In this setting, a patient’s vaccination status (exposure) will change over time, as a time-varying exposure.

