### 5.1.5 Analytical techniques

We will commence analysis by conducting descriptive analyses to visually inspect trends in vaccination delivery, age-specific COVID-19 hospitalisations and COVID-19 deaths, including by age group and sex. This will include checking the number of people who have received two doses and the length of follow-up available following the second dose by vaccine type. Including plotting Lexis diagram to afford for the correlated structure of the data (Calendar Time/Length of Follow-up)

For the analysis consisting of individuals with at least two doses, we will stratify the cohort based on the month of the second dose of each individual. The vaccination status will be classified as:

- Second dose:
  - <2 weeks
  - 2-9 weeks
  - 10-19 weeks
  - ≥20 weeks without a booster dose [Reference Period]
- Booster dose:
  - <2 week
  - 2-4 weeks
  - 5-8 weeks
  - 9-12 weeks
  - ≥13 weeks

This variable will be used to fit a Poisson regression to obtain rate ratios (RRs) and their 95% confidence intervals (CIs). If we observe overdispersion, we will consider using Negative Binomial regression models or Poisson with robust standard errors. Models will be adjusted for the relevant confounders above, including a set of dummy variables for calendar week.

The models will be fit to a dataset with all events and a random sample, without replacement, of 100 individuals per event (for hospitalisation and death, 10 for positive tests). The sample weights will be calculated to represent the sampling fraction, thus ensuring the correct calculation of the person-years at risk for the whole population.

The primary analysis for the test negative will be on individuals who are symptomatic at the time of test and the date of symptom onset is 0-10 days before the test. We will then establish the number of weeks post-vaccination for the cases and controls calculated as time between sample collection date and vaccine dose. The odds' ratio will be calculated using a logistic regression. Adjusted for: race/ethnicity, comorbidities, dummy variables for calendar week, age (five-year bands), sex. Controls will be defined based on a negative test.

We will also construct a propensity score to be tested among those in the primary cohort and use this as an inverse propensity weight.

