We will assess vaccine waning looking for statistical evidence of reducing effectiveness, we will do a trend test on the period post-vaccination from 14-27 days onwards. We will also assess an exploratory change point from 28+, 42+, 56+ days to do a linear trend test post-vaccination.

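### The SAP does not state which date puts a cohort event in a vaccination band; read naturally, early carry-over raises the 2-4 week risk and understates waning from that band

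*SAP*

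**What the plan says.** Section 5.1.2 defines the cohort outcome: "The primary outcome will be a composite outcome of time to COVID-19 hospitalisation or death". Section 5.1.1 says that "vaccination status (exposure) will change over time, as a time-varying exposure". Section 5.1.5 fits a Poisson model to bands of time since the second or booster dose. Neither section says whether the test, admission or death date decides the band.

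The positive test appears only as a qualifying condition. For admission: "COVID-19 hospitalisation will be defined as a RT-PCR confirmed positive test for SARS-CoV-2 in the 14 days prior to admission". A COVID-19 diagnosis code on the admission record also qualifies by itself, with no test and no time window. For death the condition is an interval: "within 28 days of a confirmed positive test". Footnote 2 limits Brazil to the test-to-death interval and lets Scotland also use ICD-10 codes.

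For the test-negative analysis, section 5.1.5 does fix the date: weeks since vaccination are "calculated as time between sample collection date and vaccine dose".

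On waning, section 5.1.5 states: "we will do a trend test on the period post-vaccination from 14-27 days onwards". It adds trend tests from 28, 42 and 56 days onward, which it labels exploratory. Days 0-13 after the booster form a band of their own.

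**The concern.** Objectives 3 and 4 (section 2.2) measure change from the time of maximum booster effect, so the first protected band anchors the waning estimate. If events are dated at admission or death, some events in that band belong to infections detected earlier, when the booster had not yet taken effect. The anchor is then too high. Decline from it looks smaller than it is and could vanish or reverse.

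Nothing else planned corrects the main test:
- The only alternative start of exposure named in section 5.1.7 is an earlier one (day 7).
- The exclusion of recent positives in section 3.5 is tied to study start, not to the booster date.
- The later trend starts are exploratory.
- No analysis re-dates events to the test.

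**Working it through.** The SAP gives no figure to reproduce here.

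**Inputs from the SAP.** Test-to-admission window 0-14 days; test-to-death window 0-28 days (section 5.1.2). Bands from section 5.1.5, with 2-4 weeks taken as days 14-34 because the next band is 5-8 weeks.

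**Assumptions (not in the SAP).** True rate ratio (RR) by date of positive test: 1.0 before onset of protection, then 0.20 / 0.25 / 0.35 / 0.50 in the four later bands, the last taken as days 91-146. Onset at day 14 or day 7. Constant background incidence. Lags as shown below.

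**Formula.** With r(d) the true RR for a test on day d and p(k) the probability of a lag of k days, the observed RR in a band is the average over event days t of Σ p(k)·r(t−k).

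**Even lags, by counting (event day, lag) pairs for days 14-34.**
- Admission: 21 × 15 = 315 pairs. Tests before day 14: 14 + 13 + … + 1 = 105. Tests before day 7: 7 + 6 + … + 1 = 28.
  - Onset day 14: 0.20 + 0.80 × 105/315 = 0.467.
  - Onset day 7: 0.20 + 0.80 × 28/315 = 0.271.
- Death: 21 × 29 = 609 pairs. Tests before day 14: 28 + 27 + … + 8 = 378. Tests before day 7: 21 + 20 + … + 1 = 231.
  - Onset day 14: 0.20 + 0.80 × 378/609 = 0.697.
  - Onset day 7: 0.20 + 0.80 × 231/609 = 0.503.
- Death, if nobody is boosted within 28 days after a positive test: remove the 14 + 13 + … + 1 = 105 pre-booster pairs, that is 105/609 = 0.172. This leaves 0.524 and 0.331.

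**Other lags, same formula.** Admission lags are truncated geometric. The shorter death lag is a gamma with shape 2 cut at 28 days.

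| Event and lag | 2-4 week RR, onset day 14 | onset day 7 |
|---|---|---|
| Admission, tested on the day (lag 0) | 0.20 | 0.20 |
| Admission, mean lag 2 days | 0.28 | 0.20 |
| Admission, even over 0-14 days | 0.47 | 0.27 |
| Admission, mean lag 10 days | 0.58 | 0.34 |
| Death, mean lag about 8 days, no boosting after a positive | 0.47 | 0.27 |
| Death, even over 0-28 days, no boosting after a positive | 0.52 | 0.33 |
| Death, even over 0-28 days | 0.70 | 0.50 |

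**Share of 2-4 week events with a test before day 14 (even lags).**
- Admission, onset day 14: (105/315)/0.467 = 71%.
- Admission, onset day 7: ((28 + 77 × 0.20)/315)/0.271 = 51%. At a mean lag of 2 days it is 11%.
- Death: 89% (onset day 14) and 85% (onset day 7).

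**Effect on waning (even lags, onset day 14).** Observed RRs by band are 0.467 / 0.2375 / 0.325 / 0.481 for admission and 0.697 / 0.253 / 0.300 / 0.463 for death.
- From 2-4 weeks to 13 weeks or more, truth 0.50/0.20 = 2.50: admission 0.481/0.467 = 1.03; death 0.463/0.697 = 0.66. With onset at day 7, admission is about 1.8 and death 0.92.
- From 5-8 weeks to 13 weeks or more, truth 0.50/0.25 = 2.00: admission 0.481/0.2375 = 2.03; death 0.463/0.253 = 1.83.

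**When carry-over ends.** A test-linked admission on day 28 has a test no earlier than 28 − 14 = day 14. A test-linked death on day 42 has a test no earlier than 42 − 28 = day 14.

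**The case against.** The strongest reply is that the SAP never says events are dated at admission or death, so the fault is inferred. That stands: this is an unstated date with a natural reading, not a wrong rule written down. The SAP still has to close the gap.

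The size also rests on assumptions. The 14 and 28 days are ceilings for qualifying a case, not lag distributions. If most patients are tested on admission, or protection starts by day 7 and lags are short, the admission effect is negligible (0.204 against 0.200 at a mean lag of 2 days). If positive tests are unusually rare around the booster date, carry-over would be smaller or could run the other way. This stands, and it is why only a range is given.

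The separate band for days 0-13 is a real buffer. It covers the build-up of protection, but not the test-to-event lag on top of it.

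Three stronger readings are tempting and not supported:
- A reader might infer that waning is masked altogether. The contrast from 5-8 weeks onward stays visible, and the exploratory starts at 28 and 42 days clear the windows for test-linked admissions and deaths respectively.
- A reader might infer that the 2-4 week band consists mostly of infections from before protection. That is likely for death under most of these lags, but not reliable for admission. In the composite, death sets the date only when no admission came first.
- A reader might see the two clocks as a contradiction. Section 3.1 gives the two designs different objectives, and a test is the natural index date in the test-negative design.

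**Conclusion.** The point holds as an unstated date with a predictable bias under its natural reading. The main trend test starts inside the plan's own test-to-event windows. If booster protection is still building in the first two weeks and lags are not near zero, the 2-4 week RR is too high and waning measured from that band is understated.

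For a true RR of 0.20, the apparent value is about 0.20-0.47 for admission and 0.27-0.70 for death. The upper admission figure assumes an even lag and is not a ceiling: a mean lag of 10 days with onset at day 14 gives 0.58. The primary composite should sit closer to the admission range; the separate death outcome in objective 4 is hit hardest. Onset, lags and RRs are all assumed. Severity is moderate.

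**What to change.** 1. State in section 5.1.2 or 5.1.5 which date assigns a cohort event to its vaccination band and calendar week.
2. Start the main trend test after the carry-over windows: day 28 or later for test-linked admissions, day 42 or later for test-linked deaths. The starts now labelled exploratory serve for this. For the composite, day 42 clears both; day 28 leaves only deaths without an earlier admission.
3. Add an analysis that assigns test-linked events to the band and calendar week of the qualifying sample. Keep events identified by ICD-10 code alone at their admission or death date, and say so. Tables 1 and 2 already list test dates for both countries.

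Cost: SAP wording, one recoded date and one extra model run. The main trend test loses early events. The test-date analysis runs two clocks within the composite, because code-only events (Table S1 includes U07.2, virus not identified) may have no test date. Tests in the last 28 days before the data cut lack a full outcome window there. Test date is also still later than infection date. For these reasons the test-date analysis should be reported alongside the event-date analysis and not replace it.

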## 3.4 Data sources

In Scotland, we will draw on the following databases:

- Primary care data: General Practices (n=940) for information on demographics, other population characteristics and vaccination data.
- Vaccination data: Vaccines administered in national vaccination centres and data available via the Turas Vaccination Management Tool (TVMT).
- Secondary care data: Hospital admissions through the Scottish Morbidity Record (SMR) and Rapid Preliminary Inpatient Data (RAPID).
- Laboratory test data: RT-PCR laboratory confirmed SARS-CoV-2 infection and data available via the Electronic Communication of Surveillance in Scotland (ECOSS) database.
- Mortality data from National Records Scotland (NRS)

Equivalent datasets will be used for other UK/international countries. In Brazil, we will analyse deterministically linked data provided by the Ministry of Health:

- COVID-19 vaccination (SI-PNI): Dates and types of vaccination administered, primary reason for vaccination, indigenous status, pregnancy status.
- Acute Respiratory Infection Suspected Cases (eSUS-Notifica): register of suspected and confirmed COVID-19 cases
- Severe Acute Respiratory Infection/Illness (SIVEP-Gripe): contains all hospitalisations and deaths due to severe acute respiratory illnesses, including COVID-19.

The above three databases all have whole population coverage, with returns from both public and private healthcare systems. However, data quality may vary geographically (typically data quality is better in the south of Brazil). Testing capacity has also improved over the course of the pandemic, but most improvements occurred prior to the vaccination programmes starting. In addition to the above datasets, it may be possible in the future to obtain linkage to general hospital records for patients treated within the public healthcare system (covering approximately 70% of hospitalisations in Brazil).

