# Data and Data Validation

## 4.1 Data variables available

Tables 1 and 2 lists the groupings of variables available for this study by data source. Exposure data are described in the vaccinations category. Outcome data are described in the secondary care, mortality and laboratory tests categories. The rest of categories contain data on potential confounding factors and effect modifiers.

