**Table 1: Data items/variables and data sources**

| **Data category** | **Data item** | **Data source** |
| --- | --- | --- |
| Demographic | Sex | GP |
|  | Age | GP |
| Socioeconomic | SIMD | GP |
| Other characteristics | Body Mass Index (BMI) | GP |
|  | Smoking | GP |
|  | Blood Pressure | GP |
| Geographic | Urban Rural Index (UR6); Health Board | GP |
| Clinical diagnoses | Underlying conditions  (e.g., asthma, cardiac disease, immunosuppression etc.) | GP |
| Vaccinations | Vaccine type | GP, TVMT |
|  | Vaccine dose | GP, TVMT |
|  | Vaccination date | GP, TVMT |
| Laboratory tests | RT-PCR positive SARS-CoV-2 | ECOSS |
|  | RT-PCR negative SARS-CoV-2 | ECOSS |
|  | Date of RT-PCR test | ECOSS |
| Genomic Vigilance | Date of prevalence of variants | GISAID |
| Secondary care | Hospital admissions | RAPID/SMR |
| Mortality | Death with COVID-19 as the main cause according to death certificate, or death within 28 days of a positive RT-PCR test for COVID-19 | NRS |
| Abbreviations: Scottish Index of Multiple Deprivation (SIMD), Body Mass Index (BMI), Electronic Communication of Surveillance in Scotland (ECOSS), Reverse-transcription polymerase chain reaction (RT-PCR); Turas Vaccination Management Tool (TVMT); Scottish Morbidity Record (SMR); National Records of Scotland (NRS) | | |

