**Table 2: Data items/variables and data sources in Brazil**

| **Data category** | **Data item** | **Data source** |
| --- | --- | --- |
| Sociodemographic | Sex | SI-PNI |
|  | Age | SI-PNI |
|  | Municipality-level IBP | SI-PNI |
|  | Education | (SIVEP-Gripe) |
|  | Race | SI-PNI, eSUS, SIVEP-Gripe |
|  | City |  |
| Clinical diagnoses | Underlying conditions  (Cardiac disease, chronic kidney disease, etc) | eSUS, SIVEP-Gripe |
| Vaccinations | Vaccine type | SI-PNI |
|  | Vaccine dose | SI-PNI |
|  | Vaccination date | SI-PNI |
|  | The primary reason for vaccination: 2 categories (comorbidities/other) | SI-PNI |
| Genomic Vigilance | Date of prevalence of variants | GISAID |
| Laboratory tests | Date of RT-PCR/rapid antigen test | eSUS |
|  | RT-PCR/rapid antigen positive SARS-CoV-2 | eSUS |
|  | RT-PCR/rapid antigen negative SARS-CoV-2 | eSUS |
| Secondary care  Mortality | COVID-19 hospital admission date | SIVEP-Gripe |
|  | COVID-19 death | SIVEP-Gripe/eSUS |
|  | COVID-19 death date | SIVEP-Gripe/eSUS |

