# Appendix

## **Table S1. ICD-10 codes**

| **Code** | **Description** | **Category** |
| --- | --- | --- |
| U07.1 | COVID-19, virus identified | U07.1 |
| U07.2 | COVID-19, virus not identified | U07.2 |
| Source:<https://www.who.int/classifications/icd/COVID-19-coding-icd10.pdf> | | |

1. Rapid antigen test will be evaluated only in Brazil [↑](#footnote-ref-0)
2. Brazilian data will use only time between test and date of death, while Scotland will use ICD Codes and time between test and date of death and ICD-10 codes in the death record. [↑](#footnote-ref-1)
3. The first band is 7 years: 18-24, the last band is 90+ [↑](#footnote-ref-2)

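### The test route to a COVID-19 hospitalisation stops at admission and takes RT-PCR only, and the plan does not say how Brazilian admissions are otherwise classed as COVID-19

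*SAP*

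**What the plan says.** Section 5.1.2 makes time to COVID-19 hospitalisation or death the primary outcome. An admission qualifies by either of two routes:

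- Test route: an "RT-PCR confirmed positive test for SARS-CoV-2 in the 14 days prior to admission".
- Code route: "or with ICD-10 code for COVID-19 (in any diagnostic position").

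Section 4.1 points the reader to the variable tables: "Outcome data are described in the secondary care, mortality and laboratory tests categories". For Brazilian admissions, Table 2 gives one item, "COVID-19 hospital admission date | SIVEP-Gripe". Table 1 gives "Hospital admissions | RAPID/SMR" for Scotland. Neither row names a diagnosis code.

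Section 3.4 says that SIVEP-Gripe "contains all hospitalisations and deaths due to severe acute respiratory illnesses, including COVID-19". The Brazilian test rows of Table 2 cover RT-PCR and rapid antigen results from eSUS. Footnote 2, attached to the definition of COVID-19 death, says: "Brazilian data will use only time between test and date of death". Scotland also uses ICD-10 codes there.

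Section 5.1.7 varies the hospitalisation definition in one respect only, primary diagnosis against any diagnostic position.

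**The concern.** Some patients with severe COVID-19 will have their first positive test at the hospital. A window that only looks back from admission does not clearly cover a test on the day itself and does not cover a later one. In most designs a diagnosis code picks these patients up. The plan offers that route in general terms but lists no variable that would deliver it for Brazil. The test route is also narrower than the rest of the plan: antigen results from Brazil are accepted for the test-negative design (section 3.3, footnote 1) and for previous infection (section 4.2), but not here.

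Two things are at stake. First, events for the primary composite and for the separate hospitalisation outcome (objective 4) may be lost in Brazil, which costs precision. Second, the outcome would depend on whether a person sought a test before admission. Section 5.1.2 already treats the infection results as tentative because of differential ascertainment, and this dependence would carry the same problem into the primary outcome. The working definition could also differ between two countries whose analyses the Introduction wants harmonised.

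**Working it through.** **Step 1: follow a Brazilian patient through the rule, using only the listed data.**

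| Patient | Test route | Code route | Death limb |
| --- | --- | --- | --- |
| RT-PCR positive 1 to 14 days before admission | met | not needed | – |
| First RT-PCR positive on the admission day | unclear | no code listed | if death within 28 days of the test |
| First RT-PCR positive after admission | not met | no code listed | if death within 28 days of the test |
| Antigen positive only, before admission | not met | no code listed | if death within 28 days of the test |

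The death limb asks for a confirmed positive test and does not name the type of test, so I have let antigen results count there. Patients who enter through it do so at the date of death, not of admission. Survivors in the last two rows meet no written route with the listed data.

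**Step 2: is another criterion written down?** SIVEP-Gripe covers all severe acute respiratory illness, so some rule must pick out the COVID-19 admissions. The Table 2 item is already called "COVID-19 hospital admission date", which suggests that a classification exists. Section 5.1.2 does not mention it, and no field or code is named.

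**Step 3: size.** The SAP has no figure to reproduce: it gives neither event counts nor the timing of tests around admission. All shares below are assumptions.

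*Equal loss.* If a fraction f of hospitalisation events is lost in every exposure group, the RR is unchanged and the standard error of log RR is multiplied by 1/√(1 − f):

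- f = 0.20: 1/√0.80 = 1.12, up 12%
- f = 0.40: 1/√0.60 = 1.29, up 29%
- f = 0.60: 1/√0.40 = 1.58, up 58%

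*Unequal loss.* Let p₁ and p₀ be the shares of boosted and unboosted admissions with a qualifying pre-admission test. The observed RR is the true RR × p₁/p₀:

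- p₁ = 0.60, p₀ = 0.50: 0.60/0.50 = 1.20 (booster looks less protective)
- p₁ = 0.50, p₀ = 0.60: 0.50/0.60 = 0.83 (booster looks more protective)

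These figures are for hospitalisation events and assume that every admission without a pre-admission positive is missed. In the composite, patients recovered through the death limb reduce the loss.

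**Step 4: would the plan detect it?** No. Section 5.1.7 does not vary the test window or the type of test. Adjusting for calendar week (sections 5.1.3 and 5.1.5) handles changes in testing over time but not a difference in testing between boosted and unboosted people in the same week.

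**The case against.** The best reply is that the documents do not show that any event will be lost. Much of it stands:

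- The code route is joined by an or, and has neither a country nor a timing limit.
- A code missing from Table 2 is weak evidence, because Table 1 lists none for Scotland either, although sections 5.1.2 and 5.1.7 rely on diagnostic position.
- Footnote 2 drops ICD codes for Brazilian deaths only. Nothing similar is attached to admissions.
- The Table 2 item is already labelled as a COVID-19 admission, so the register's own classification may be the intended criterion.
- Tests on the admission day are ambiguous, not excluded, and in-hospital positives who die within 28 days still enter the composite.

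A reader might therefore infer too much in saying that ICD codes are unavailable in Brazil, or that Brazilian patients diagnosed in hospital are never events. The documents do not support either statement.

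The reply does not close the gap. If the register's classification is what Brazil will use, section 5.1.2 omits the operative rule for the primary outcome. If it is not, the written rule misses the survivors identified above. In both cases the test route has no post-admission window and leaves out antigen tests.

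**Conclusion.** The point holds as a defect in how the primary outcome is fixed, not as a demonstrated loss of events. On the literal text, Brazilian patients first positive after admission, or positive by antigen only, may not be counted as hospitalisations unless they die within 28 days of a positive test. Whether they are counted in practice depends on a classification that the plan does not state.

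Equal loss would cost precision only: 12% to 58% on the standard error for an assumed 20% to 60% of hospitalisation events lost. Unequal pre-admission testing by booster status would bias the RR, and the documents give no ground for predicting the direction; the illustration gives 1.20 one way and 0.83 the other. Because neither size nor direction can be known from the plan, the rule should be settled before the analysis. The change is worth making, since it concerns the primary outcome and costs little.

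**What to change.** In section 5.1.2:

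1. Count a first positive test from 14 days before admission through the admission day and a short fixed window after it (two days, for example; the team should choose and justify the length).
2. State that the qualifying test is RT-PCR, or in Brazil RT-PCR or rapid antigen.
3. For Brazil, name the SIVEP-Gripe field or classification that stands in for the ICD-10 route, and add it to Table 2.

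In section 5.1.7, keep the pre-admission-only rule as a sensitivity analysis, so that readers can see whether the RR depends on where the window ends.

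The cost is a change of SAP wording. The downside is that a small number of hospital-acquired infections may be counted as COVID-19 admissions, which a short window limits.

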### 5.1.3 Potential confounders

We will consider adjusting for age, sex, socioeconomic position, geography and where possible, comorbidities. More specifically, we anticipate adjusting for the following confounders in Scotland: age (five-year bands^^[[3]](#footnote-2)^^), sex, socioeconomic position (SEP) measured by quintiles of the Scottish Index of Multiple Deprivation (SIMD) (1 refers to most deprived and 5 refers to least deprived), residential settlement measured by the urban/rural 6 fold classification (1 refers to large urban areas and 6 refers to small remote rural areas), household size, number and types of comorbidities commonly associated with COVID-19 illness (asthma, chronic kidney disease, liver cirrhosis, chronic neurological condition, heart failure, diabetes (type 1 and type 2), dementia, coronary heart disease), risk factors (smoking status, blood pressure, body mass index (BMI)) and Health Board.

In Brazil, we anticipate adjusting for age (five-year bands), sex, the primary reason for vaccination, race/ethnicity and calendar week will be accounted for within the statistical models.

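### The cohort model for positive tests has no protection against differential testing: no listed adjustment set measures testing tendency, although both countries' registers hold dated negative tests.

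*SAP*

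**What the plan says.** Section 5.1.2 lists RT-PCR-confirmed infection as a secondary outcome and warns: "We anticipate the RT-PCR confirmed SARS-CoV-2 infection results to be more susceptible to bias arising from differential ascertainment". The response stated there is a caveat on interpretation: "and therefore anticipate treating these results as more tentative".

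Infection is analysed in two ways:

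- **Test-negative design.** Section 3.1 assigns the infection objective (Objective 2 in section 2.2) to this design. Under section 5.1.5 its primary analysis takes symptomatic people whose symptoms began 0 to 10 days before the test.
- **Cohort.** The sampling rule for the Poisson models in section 5.1.5 sets 100 sampled individuals per event "for hospitalisation and death, 10 for positive tests". A cohort model for positive tests is therefore planned as well.

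The covariates are given in three places. Section 5.1.3 opens with "We will consider adjusting for age, sex, socioeconomic position, geography and where possible, comorbidities" and then details a Scottish list. For Brazil it says "In Brazil, we anticipate adjusting for age (five-year bands), sex, the primary reason for vaccination, race/ethnicity and calendar week". For the test-negative logistic model, section 5.1.5 says "Adjusted for: race/ethnicity, comorbidities, dummy variables for calendar week, age (five-year bands), sex".

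On the data, Table 1 lists "RT-PCR negative SARS-CoV-2" from ECOSS and Table 2 lists "RT-PCR/rapid antigen negative SARS-CoV-2" from eSUS. Each table also lists positive results and the test date.

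**The concern.** A rate of positive tests is the product of how often people are infected and how often infections are detected. In a cohort, a person who tests often has more infections recorded than an equally infected person who seldom tests. If testing tendency is related to when, or whether, a person was boosted, the rate ratio absorbs the difference.

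The waning question is especially exposed. The models carry calendar-week dummies, so within a given week the post-booster bands contrast people boosted at different dates, and those in the late bands were boosted earlier. If early uptake goes with more testing, for instance through work or care settings (neither is a listed covariate), the late-band rate ratio rises although protection has not changed. The trend test in section 5.1.5 looks for that same pattern. Section 3.6 expects millions of boosted people in Brazil, so such a bias could come with a narrow confidence interval.

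**Working it through.** The plan states no figure on this point, so there is nothing to reproduce. The check is textual, followed by an illustration on assumed values.

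**1. Is there a testing term in any listed set?**

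| Source | Terms listed | Testing tendency? |
|---|---|---|
| 5.1.3, Scotland | age, sex, deprivation, urban/rural class, household size, comorbidities, smoking, blood pressure, BMI, Health Board | no |
| 5.1.3, Brazil | age, sex, reason for vaccination, race/ethnicity, calendar week | no |
| 5.1.5, test-negative model | race/ethnicity, comorbidities, calendar week, age, sex | no |
| 5.1.5, propensity score | covariates not listed | neither stated nor ruled out |
| 4.2, constructed variables | previous infection; interval from second dose to booster | no: previous infection is built from positive tests |

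Table 2 gives Brazil's reason for vaccination only two categories (comorbidities or other), so it cannot pick out regularly tested workers.

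**2. Could a testing term be built?** Yes. Tables 1 and 2 list dated negative and positive tests. Section 3.5 already applies person-level test history: it drops a negative test that falls within 14 days of a previous negative, and any test within 90 days of a previous positive. Section 4.2 already looks back from 15 September 2021 in the cohort.

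**3. Which analysis is unprotected?** The test-negative analysis compares tested people with tested people, all symptomatic in its primary form. The cohort Poisson model counts positives over everyone's person-time. Its sampling weights restore the person-years at risk but do nothing about detection.

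**4. How large might the distortion be?** Let *p1* be the share of frequent testers in the late band, *p0* their share in the comparison band, and *r* the ratio of their detection rate to that of others. With the same true infection risk in both groups,

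distortion = (1 + *p1*(*r* − 1)) / (1 + *p0*(*r* − 1)).

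All inputs below are assumptions; the SAP supplies none of them.

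| p1 | p0 | r | Distortion |
|---|---|---|---|
| 0.10 | 0.05 | 2 | 1.10 / 1.05 = 1.05 |
| 0.15 | 0.05 | 3 | 1.30 / 1.10 = 1.18 |
| 0.20 | 0.05 | 3 | 1.40 / 1.10 = 1.27 |

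The direction depends on which band holds more frequent testers. Swapping *p1* and *p0* in the last row gives 1.10 / 1.40 = 0.79, which would hide waning.

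The consequence can also be put in terms of testing alone: observed rate ratio = true rate ratio × testing ratio. Take a true rate ratio constant at 0.50 (assumed) and a testing ratio against the reference period that drifts from 1.00 to 1.25 with time since booster (assumed). The observed value moves from 0.50 × 1.00 = 0.50 to 0.50 × 1.25 = 0.625. Apparent effectiveness falls from 50% to 37.5% with no true waning.

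**The case against.** The strongest reply is that the plan does act on this bias. A reader of section 5.1.2 alone might infer that calling the results tentative is its only response. The document as a whole does not support that. Objective 2 has its own test-negative design, its symptomatic restriction removes asymptomatic screening from the primary analysis, and the exclusions in section 3.5 limit the weight of frequent testers. This stands, and it confines the gap mainly to the cohort model. That model is itself narrow: the cohort objectives (3 and 4) concern severe outcomes, and infection enters through the secondary list, if event numbers allow, and through the sampling rule.

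Other mitigations are weaker. Adjustment for previous infection is only a possible sensitivity analysis (section 5.1.7), uses no negative tests, and measures past infection rather than readiness to test. The propensity score might contain a testing term, but nothing commits it to one. Negative-control outcomes (section 5.1.8) are conditional, and the example given, non-COVID hospitalisation, would not directly reveal differences in SARS-CoV-2 testing.

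Two further objections are sound. The distortion formula is crude: stratification by month of second dose, calendar week, age and comorbidities may absorb part of the link between booster timing and testing. And a count of all tests would mix testing tendency with previous infection, and would not mean the same in both countries. Table 1 lists RT-PCR only for Scotland, whereas Brazil also has rapid antigen tests. Section 3.4 describes eSUS-Notifica as a register of suspected and confirmed cases, and warns that Brazilian data quality varies by region. These objections shape the fix; they do not remove the need for it.

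**Conclusion.** The point holds for the cohort Poisson model of positive tests. The plan expects differential ascertainment of infection, no listed adjustment set measures testing tendency, and the data to build such a measure are already listed. The test-negative analysis is partly protected by design, so there the omission is secondary.

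The size is unknown. The range 1.05 to 1.27 rests wholly on assumed shares of frequent testers (10 to 20% against 5%) and an assumed two- to threefold detection rate, before any adjustment. The upward direction rests on the further assumption that people boosted earlier test more.

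Three stronger readings should be resisted. The plan does not call differential ascertainment its main threat; it says only that infection results are more susceptible to it. It does not ignore earlier tests altogether, since previous infection is built from them. And nothing shown here bears on the primary outcome of hospitalisation or death: the plan's warning concerns infection, and so does this point. The outcome is secondary and already labelled tentative, but that label shows neither the direction nor the size of the bias, so a pre-specified adjustment is worth making.

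**What to change.** - **Cohort infection model and its propensity score (5.1.3, 5.1.5):** add a baseline covariate for the number of negative SARS-CoV-2 tests in a fixed window before 15 September 2021. State the window length in the SAP (12 months, for example). Because it predates the study start, the covariate cannot be a consequence of booster doses given during the study.
- **Categories:** set them within each country, because test types and registers differ.
- **Previous infection:** enter the section 4.2 variable separately alongside it, so that testing tendency and past infection are not merged.
- **Test-negative design:** add the covariate as a sensitivity analysis (5.1.7).
- **Section 5.1.2:** say that the cohort infection results are adjusted for prior testing and that residual ascertainment bias remains.

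The cost is one derived variable from data already listed, plus SAP wording; the extra model terms are negligible in a cohort of millions. The limitation is that in Brazil the count may partly reflect earlier suspected illness and regional access to testing, so it will reduce the bias rather than remove it.
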